## Abstract

Adolescents are increasingly exposed to sedentary behaviours and poor ergonomic environments that may adversely affect posture, aerobic capacity, and psychological well-being. This article describes a standardized protocol for implementing and evaluating an 8-week Posture Education Program (PEP) among high school students aged 14–17 years using a randomized controlled trial design. The intervention includes postural awareness, core strengthening, ergonomic correction, guided movement, and reflective behavioural activities delivered during physical education sessions. The control group will continue standard physical education without posture-specific training. The program was developed using the ADDIE instructional framework, while the International Classification of Functioning, Disability and Health framework guided outcome selection. Primary outcomes include postural alignment, aerobic capacity, and lung function. Secondary outcomes include physical activity, psychological well-being, and ergonomic knowledge and behaviour. This protocol provides a reproducible framework for school-based posture education interventions and integrates multidimensional assessment of postural, cardiorespiratory, behavioural, and psychological outcomes within a school-based adolescent population.

Structured 8-week school-based posture education intervention integrated into physical education sessions.

Multidimensional assessment of posture, aerobic capacity, lung function, and psychological well-being.

Reproducible randomized controlled trial protocol guided by ADDIE and ICF frameworks.

Specifications table

**Table utbl0001:** 

**Subject area**	Medicine and Dentistry
**More specific subject area**	School-based physiotherapy / adolescent posture intervention
**Name of your method**	Posture Education Program (PEP) for High School Students
**Name and reference of original method**	Developed using the ADDIE instructional design model and informed by ergonomic and posture education literature.
**Resource availability**	Peak flow meter, automatic blood pressure monitor, posture grid, IPAQ-SF, GHQ-28, KAP questionnaire, stopwatch, standardized 6-minute walk test (6MWT) track setup, and intervention session materials.

## Background

Adolescents are [1] increasingly exposed to lifestyle factors that contribute to suboptimal postural alignment, including prolonged screen use, sedentary behaviour, and inadequate ergonomic awareness in school and home environments [2,3]. During secondary school years, students often engage in prolonged static sitting and device-based learning, which may influence musculoskeletal development and postural habits. Emerging evidence suggests that postural deviations in adolescents may be associated not only with musculoskeletal discomfort but also with altered respiratory function and reduced pulmonary efficiency [1,4]. In addition, reduced physical activity and increased sedentary behaviour during adolescence have been linked to cardiovascular risk profiles and psychosocial stress indicators [3,5]. These findings highlight the potential multidimensional health implications of sustained postural imbalance during formative developmental years.

Several corrective exercises and posture-focused interventions have been implemented in adolescent populations. For example, corrective exercise programs focusing on thoracic kyphosis and upper-quadrant alignment have demonstrated improvements in postural parameters and body image among adolescents with hyperkyphosis [6]. Nevertheless, structured, school-based posture education programs designed for preventive use in generally healthy adolescents remain limited. Furthermore, few protocols have integrated postural education with objective measures of cardiorespiratory health and standardized psychological well-being assessments within a single framework. Existing school-based interventions have commonly focused on general physical activity, fitness promotion, corrective exercise, or ergonomic awareness as separate components. However, few published protocols have combined posture education, progressive postural exercise, ergonomic behaviour training, and psychological well-being assessment within a single school-based randomized controlled trial. In addition, many posture-related interventions focus on adolescents with existing postural deviations, whereas preventive programs for generally healthy high school students remain less clearly described. The present protocol addresses this gap by providing a structured, theory-informed, and reproducible intervention that can be integrated into scheduled physical education sessions without major disruption to the school timetable. Several posture-focused and corrective exercise interventions have been conducted among adolescent populations; however, their intervention approaches, outcome domains, and implementation contexts vary considerably. For example, Mokhtaran et al [6] evaluated two corrective exercise approaches among adolescent schoolgirls with hyperkyphosis over an 8-week intervention period using upper-quadrant posture and body image as primary outcome measures. The study reported improvements in postural alignment and body image following the intervention. However, the study focused primarily on adolescents with existing postural deviations and did not assess cardiorespiratory outcomes, ergonomic behaviour, or psychological well-being within a preventive school-based framework.

Similarly, previous school-based physical activity interventions among adolescents have demonstrated improvements in aerobic fitness and physical activity participation [7]. Nevertheless, many of these interventions primarily focused on general physical activity promotion and cardiovascular fitness rather than structured posture education, ergonomic correction, or posture-related behavioural modification. In addition, posture-related intervention studies frequently assessed musculoskeletal or alignment outcomes independently without integrating multidimensional physiological and psychological assessments Fig. 1.

**Fig. 1 fig0001:**
[figure not shown]
Flow chart of the study.

Previous studies have also utilized posture assessment methods, respiratory outcome measures, and exercise capacity testing separately in adolescent populations [[8], [9], [10],^4^]. However, few published protocols have combined posture education, progressive postural exercise, ergonomic behaviour training, and multidimensional assessment of postural, cardiorespiratory, behavioural, and psychological outcomes within a single school-based randomized controlled trial. Furthermore, preventive posture education interventions targeting generally healthy adolescents within routine physical education settings remain limited and insufficiently described in the literature.

The present protocol addresses these gaps by providing a structured, theory-informed, and reproducible posture education intervention that can be integrated into scheduled physical education sessions without major disruption to the school timetable.

The novelty of the present protocol lies in its integration of posture education, ergonomic behaviour training, progressive postural exercise, and multidimensional outcome assessment within a structured school-based randomized controlled trial. The protocol combines objective assessment of posture, aerobic capacity, and lung function with behavioural and psychological outcome measures . In addition, the use of the ADDIE instructional framework supports systematic intervention development and implementation planning, while the ICF framework supports alignment of intervention components with body functions, activity, participation, and contextual domains [11]. This combined theory-informed approach provides a reproducible model for evaluating posture education as a preventive intervention among generally healthy high school students.

There is a need for a structured, reproducible protocol that combines posture education with multidimensional outcome assessment aligned with contemporary health models. The posture education program (PEP) was developed using the Analysis, Design, Development, Implementation, and Evaluation (ADDIE) instructional framework and validated through expert consensus using a Delphi process. The conceptual structure of the program is informed by the International Classification of Functioning, Disability, and Health (ICF) framework [11], ensuring alignment across domains of body functions, body structures, activity, and participation. The ADDIE framework was used to systematically guide the development and implementation of the intervention, while the ICF framework informed the classification of outcome domains, ensuring that intervention components target measurable changes in body functions, activity, and participation.

The purpose of this protocol article is to describe, in detail, the implementation procedures and standardized assessment methods for a randomized controlled trial evaluating the PEP in adolescents aged 14–17 years in the United Arab Emirates. The protocol provides sufficient methodological detail to enable replication in similar educational settings and supports comprehensive evaluation of posture, aerobic capacity, psychological well-being, and ergonomic knowledge.

## Method details

### Study design

This study employs a two-arm, parallel-group, randomized controlled trial (RCT) design with a 1:1 allocation ratio. The intervention group receives the PEP delivered during scheduled physical education sessions, replacing the standard PE content, while the control group continues with the standard PE curriculum alone.

The protocol was developed in accordance with the Standard Protocol Items: Recommendations for Interventional Trials (SPIRIT) guidelines for clinical trial protocols. Although the intervention is delivered in a school setting, participant-level randomization was selected because this study is designed as a preliminary randomized controlled protocol evaluating the feasibility and effectiveness of the PEP within scheduled physical education sessions. Both groups will receive sessions of equal duration and frequency to minimize attention-related bias. However, due to the educational and exercise-based nature of the intervention, complete blinding of participants and educators is not feasible.

### Study location

A secondary school in the United Arab Emirates.

### Sample size calculation

Sample size was calculated using G*Power version 3.1 for a mixed-design repeated-measures ANOVA examining the group × time interaction. Peak expiratory flow rate (PEFR) was selected as the primary outcome for sample size estimation. The selection of the effect size was informed by a previous randomized controlled trial investigating the effect of McKenzie exercises on pulmonary function among individuals with forward head posture, which demonstrated significant improvements in PEFR following the intervention [12]. To avoid overestimating the intervention effect and to ensure a conservative estimate for the present school-based posture education programme, a medium effect size (f = 0.25), alpha level of 0.05, and statistical power of 0.80 were used for the sample size calculation. The analysis indicated that a minimum of 28 participants per group was required. Allowing for an anticipated attrition rate of 20%, the target sample size was increased to 35 participants per group, resulting in a total planned sample of 70 students.

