### Outcome measures

Standardized outcome assessments will be conducted at baseline (Week 0), mid-intervention (Week 4), and post-intervention (Week 8). All assessments will be performed at approximately the same time of day to minimize physiological variability.

Primary outcome measures include lung function, postural alignment, and functional aerobic capacity. Postural alignment will be assessed using standardized posture grid analysis based on validated observational criteria [9,10]. Participants will stand in a standardized anatomical position in front of a calibrated posture grid, and alignment will be evaluated relative to vertical and horizontal reference lines to identify deviations in head position, shoulder symmetry, and spinal curvature. Posture grid assessment has demonstrated acceptable inter-rater and intra-rater reliability in previous adolescent posture assessment studies [9,10]. Standardized assessor training and assessment procedures will be implemented to support consistency during data collection.

Functional aerobic capacity will be assessed using the six-minute walk test (6MWT) conducted according to established guidelines [14]. Participants will be instructed to walk as far as possible along a standardized corridor for six minutes with consistent verbal encouragement. The total distance covered in meters will be recorded as the outcome measure. In addition to walking distance, participants’ heart rate, blood pressure, and oxygen saturation (SpO₂) will be measured before, during, and after the test. Perceived exertion will be assessed using Borg’s Rating of Perceived Exertion (RPE) scale, a validated tool used to measure subjective exercise intensity during physical activity [15]. The 6MWT has demonstrated good reliability and validity for assessing submaximal exercise capacity in adolescent populations [8,16]. Changes in walking distance will be interpreted alongside baseline performance and age-appropriate normative reference values derived from healthy children and adolescents [17].

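### The minimum of 28 per group at 80% power is not reproduced by the named G*Power test at its default settings, which return 28 in total

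*Protocol article*

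**What the plan says.** The Sample size calculation section of the protocol article identifies the method: "Sample size was calculated using G*Power version 3.1 for a mixed-design repeated-measures ANOVA examining the group × time interaction". Peak expiratory flow rate (PEFR) is the outcome used for sizing. The inputs are given as "a medium effect size (f = 0.25), alpha level of 0.05, and statistical power of 0.80 were used for the sample size calculation", and the section calls the resulting estimate conservative. The result is "The analysis indicated that a minimum of 28 participants per group was required". After a 20% attrition allowance, "the target sample size was increased to 35 participants per group, resulting in a total planned sample of 70 students".

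Two further inputs stand elsewhere in the article. Study design describes a "two-arm, parallel-group, randomized controlled trial (RCT) design with a 1:1 allocation ratio". Outcome measures and Data analysis both give three assessments: baseline, Week 4 and Week 8.

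The article does not state the correlation among repeated measures, the nonsphericity correction epsilon, or which of G*Power's effect-size definitions was used.

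**The concern.** G*Power reports a total sample size for this test. At the default settings that total is 28, the same number that the article gives for each group. The published size and the published power then do not belong together.

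This calculation is the only basis that the article gives for enrolling 70 adolescents. A reader or ethics committee who re-runs it at the defaults gets half the stated minimum. Under another effect-size option they get almost one and a half times the stated minimum. The article presents itself as a reproducible framework, so the figure may be copied into later trials.

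**Working it through.** **Inputs from the article.** f = 0.25, alpha = 0.05, power = 0.80 and the group × time interaction (Sample size calculation); k = 2 groups at 1:1 (Study design); m = 3 time points (Outcome measures).

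**Inputs assumed.** Correlation rho = 0.5, epsilon = 1 and the default effect-size option. All three are then varied.

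**Formula.** Power comes from the noncentral F distribution, where N is the total:

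- lambda = f² × N × m × epsilon / (1 − rho)
- df1 = (k − 1)(m − 1) × epsilon
- df2 = (N − k)(m − 1) × epsilon

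The required N is the smallest even total with power of at least 0.80.

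**1. Default settings.**

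- N = 26: lambda = 0.0625 × 26 × 3 / 0.5 = 9.75, df 2 and 48, power 0.778.
- N = 28: lambda = 0.0625 × 28 × 3 / 0.5 = 10.5, df 2 and 52, power 0.812.

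The answer is 28 in total, or 14 per group. With 20% attrition, 14 / 0.8 = 17.5, so 18 per group and 36 in total.

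**2. Power of the published size at the same settings.**

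- N = 56: lambda = 21.0, df 2 and 108, power 0.987.
- N = 70: lambda = 26.25, df 2 and 136, power 0.997.

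**3. Other correlations, epsilon = 1.**

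| rho | Total N for 80% power |
|---|---|
| 0 | 54 |
| 0.1 | 48 |
| 0.2 | 44 |
| 0.3 | 38 |
| 0.4 | 34 |
| 0.5 | 28 |
| 0.6 | 24 |
| 0.7 | 18 |
| 0.8 | 12 |

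No row gives 56. At rho = 0 the required total is 54 (power 0.809), and 56 gives 0.824.

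**4. Epsilon below 1.** With three time points epsilon cannot fall below 0.5.

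| rho | epsilon | Total N | Power at that N |
|---|---|---|---|
| 0.1 | 0.8 | 56 | 0.802 |
| 0.2 | 0.7 | 56 | 0.811 |
| 0.4 | 0.5 | 54 | at least 0.80 |
| 0.5 | 0.5 | 44 | 0.801 |

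So 56 can be reached, but only by combining a correlation below the default with an epsilon below 1. At rho = 0.5 even the lowest admissible epsilon gives 44.

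**5. Other effect-size options (m = 3, epsilon = 1).**

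| Option | lambda | Total N | Power at 56 | Power at 70 |
|---|---|---|---|---|
| As in SPSS | f² (N − k)(m − 1) | 82 | 0.63 | 0.74 |
| Cohen | f² N (m − 1) | 80 | 0.64 | 0.75 |

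Neither gives 56 in total, or 0.80 power at 56 or 70.

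**6. Attrition step.** 28 / 0.8 = 35 per group and 2 × 35 = 70. This step is correct and consistent with the article's own minimum.

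**The case against.** The strongest reply is that the article's stated inputs do not fix any sample size. The answer also depends on rho, epsilon and the effect-size option, and a condensed article may leave these to the full protocol. The figure of 28 in total rests on default settings that the article does not say were used. Data analysis foresees a sphericity violation and a Greenhouse–Geisser correction, so an epsilon below 1 cannot be dismissed. With rho 0.1 and epsilon 0.8, or rho 0.2 and epsilon 0.7, the stated 28 per group is exactly right. A deliberately low correlation might also be what the authors meant by a conservative estimate.

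Much of this stands, and it rules out three stronger readings that a reader might infer.

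- **That no settings can produce 28 per group.** This is true only at epsilon = 1.
- **That the program's output was 28 in total and was misread.** The match is striking, but the article does not show the output.
- **That the trial is underpowered.** This would follow only if the SPSS or Cohen option had been used, and nothing in the article says so.

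The missing settings are not themselves the finding. What remains is that a result presented as the output of a named program is not what that program returns at its defaults. The settings that would rescue it require values from the same student, weeks apart, to be only weakly related. That fits poorly with Outcome measures, which describes PEFR test–retest reliability as acceptable and uses the best of three efforts. The article gives no correlation, so this last step is a judgement.

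**Conclusion.** The point holds as a mismatch between a stated sample size and a stated power, conditional on the default settings. At rho 0.5 and epsilon 1 the minimum is overstated by a factor of two (56 against 28 in total), and the power that goes with 56 completers is about 0.99 in place of 0.80. If rho was low and epsilon reduced, the published figure could be right, but then the unusual settings need to be stated. If another effect-size option was used, 56 falls short of the 80 to 82 required.

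On the default reading the consequence is a trial larger than its stated power needs, by 34 students (70 against 36 after attrition). Nothing in this point argues for changing the number enrolled.

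**What to change.** Retrieve the saved G*Power output and re-run the calculation. Then revise the sample size paragraph in one of two ways:

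- correct the minimum to the total that the program returned, which is 28 in total if the defaults were used; or
- keep 28 per group and restate the power that 56 completers and 70 randomised give for the planned group × time test.

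In either case state rho, epsilon and the effect-size option. If a low rho and a reduced epsilon were entered, say why they suit repeated PEFR. The paragraph should say that the output was 28 in total only if the saved output confirms it.

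The 70 randomised and the attrition step can stay as they are. The cost is one re-run and the rewording of one paragraph.

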### Inclusion and exclusion criteria

Participants eligible for inclusion will be students aged 14 to 17 years who provide written parental or legal guardian consent and student assent prior to participation, and who are willing and able to attend the scheduled posture education program sessions and outcome assessment time points.

Students with diagnosed cardiovascular, respiratory, musculoskeletal, or neurological conditions that may limit safe participation in physical activity, such as severe scoliosis requiring medical treatment, uncontrolled asthma, recent musculoskeletal injury, or neurological disorders affecting mobility, will be excluded.

Eligibility screening will be conducted by the research team prior to baseline assessment.

### Randomization and blinding

Participants will be randomly assigned to either the intervention or control group using a computer-generated block randomization sequence with variable block sizes of four and six to ensure balanced allocation between groups throughout the recruitment period while minimizing predictability of group assignment. Randomization will be performed by an independent researcher not involved in data collection or intervention delivery. Allocation concealment will be ensured using sequentially numbered sealed opaque envelopes prepared before participant enrolment. Outcome assessors will be blinded to group allocation to minimize measurement bias. Participants will not be informed of the study hypotheses and will attend sessions as part of their scheduled school activities to minimize expectation bias. To ensure blinding, assessors will not be involved in intervention delivery and will be instructed not to ask participants about their group allocation. Participants will also be reminded not to disclose their group assignment during assessments. Any accidental unblinding during outcome assessment procedures will be documented.

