### Intervention

Participants allocated to the intervention group will receive the 8-week PEP delivered during scheduled physical education sessions, consisting of one 50-minute session per week. To ensure feasibility within the school setting and minimize disruption to academic activities, sessions will be conducted during scheduled physical education periods. Each session will involve approximately 15 to 20 students and will be supervised by a trained educator to ensure correct exercise performance, safety, and adherence to the intervention protocol. Both groups will receive sessions of equal frequency and duration (one 50-minute session per week); however, only the intervention group will receive structured posture education content. The program includes postural awareness training, core strengthening exercises, ergonomic correction strategies, guided movement activities, and breathing and relaxation techniques. Participants’ baseline posture control, and core endurance will be assessed during the initial session to guide appropriate exercise starting levels. All participants will begin with low-intensity posture-focused activation exercises to ensure familiarization with correct movement techniques.

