## Limitations

This study has several limitations. First, the intervention duration is limited to eight weeks, which may restrict evaluation of long-term behavioural changes and sustained physiological effects. Second, some secondary outcomes rely on self-reported measures, including the IPAQ-SF and GHQ-28, which may be influenced by recall bias, social desirability bias, and variability in adolescents’ interpretation of questionnaire items [19,20]. Third, because the intervention is delivered within a school setting, contamination between intervention and control participants may occur through peer interaction outside intervention sessions. Fourth, complete blinding of participants and educators was not feasible due to the educational and exercise-based nature of the intervention. Fifth, although participant-level randomization is used, the group-based school delivery format may introduce teacher-level or class-level influences that are not fully controlled. Finally, findings may have limited generalizability beyond generally healthy adolescents aged 14–17 years within the specific cultural and educational context of the United Arab Emirates. Future studies may consider cluster-randomized designs to better minimize potential contamination and class-level influences within school-based interventions, as well as longer follow-up periods and implementation across multiple schools and educational settings.

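### The block list balances the arms over recruitment time but not over the PE periods or classes in which both arms are delivered; stratify the list and put the stratum in the model

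*Protocol article*

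**What the plan says.** All of this is in the protocol article.

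- **Study design:** a two-arm "randomized controlled trial (RCT) design with a 1:1 allocation ratio". It adds that "participant-level randomization was selected because this study is designed as a preliminary randomized controlled protocol". PEP replaces the usual PE content for the intervention group; the control group keeps standard PE.
- **Study location:** "A secondary school in the United Arab Emirates". The numbers of classes, PE teachers and PE periods are not given.
- **Inclusion and exclusion criteria:** "students aged 14 to 17 years who provide written parental or legal guardian consent and student assent", so several school years may be involved.
- **Randomization and blinding:** a "computer-generated block randomization sequence with variable block sizes of four and six to ensure balanced allocation between groups throughout the recruitment period", with sealed envelopes prepared before enrolment. No stratification factor is named.
- **Intervention:** "sessions will be conducted during scheduled physical education periods", and "Each session will involve approximately 15 to 20 students". No rule links the allocation to the forming of these groups.
- **Data analysis:** a mixed-design repeated-measures ANOVA of group by time, with no term for class or PE period.
- **Limitations:** "the group-based school delivery format may introduce teacher-level or class-level influences that are not fully controlled".

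**The concern.** Permuted blocks on one list keep the arms level in order of enrolment. In this trial the calendar of enrolment matters little. The PE period in which a student is taught matters more, because it goes with class, time of day, usual teacher and perhaps school year. The article sees a class-level influence and records it as a limitation, but neither the allocation nor the stated model does anything about it.

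If more students of one period land in PEP than in control, whatever happens in that period over the eight weeks falls unequally on the arms. Across repeated trials this averages out. In a single trial of 70 it adds noise to the comparison, and it can leave one PEP group crowded and another thin.

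**Working it through.** **Inputs.** From Sample size calculation: 28 per group, 20% attrition, 35 per group, 70 in all. From Randomization and blinding: blocks of 4 and 6. From Intervention: sessions of about 15 to 20. Two inputs are not in the article and are assumed over a range: the number of equal-sized periods or classes (two to four), and the order of enrolment (fully mixed, or class by class).

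**Step 1: the plan's own figure.** 28 / (1 − 0.20) = 35 per group, so 70 in total. This reproduces. About 35 PEP students must therefore be placed in sessions, for example 35 / 2 = 17.5 per session if there are two.

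**Step 2: two periods of 35, mixed enrolment.** If c students of a period are in PEP, the arm difference in that period is |2c − 35|. A difference of 5 or more means c ≤ 15 or c ≥ 20. The stated block scheme was simulated 40,000 times per scenario:

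| Two periods of 35 | One list, mixed order | One list, class by class | Stratified list |
|---|---|---|---|
| Arm difference of 5 or more in a period | 37% | under 1% | 0% |
| A PEP group outside 15–20 | 17% | 0% | 0% |
| A PEP group outside 14–21 | 6% | 0% | 0% |
| A PEP group outside 13–22 | 2% | 0% | 0% |

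As a check without simulation, suppose exactly 35 of the 70 are in PEP and the mixing is complete. Then c is hypergeometric (70 students, 35 in PEP, 35 in the period), which gives 34% for a difference of 5 or more, 15% outside 15–20 and 6% outside 14–21. The simulated figures are slightly higher because an incomplete last block lets the PEP total vary from 34 to 36.

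**Step 3: more periods.** With four periods (18, 18, 17, 17) and mixed order, a difference of 5 or more in at least one period occurs in 57% of trials. Class by class it is again under 1%, and stratified it is 0%. The average PEP group per period is 35 / 3 ≈ 12 with three periods and 35 / 4 ≈ 9 with four, under any of the schemes. Groups of 15 to 20 then need pooling across periods, whatever the list looks like.

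**Step 4: the largest difference under stratification.** Every complete block is balanced. The worst case is an incomplete block of 6 whose first three places all go to one arm, a difference of 3. The simulated maximum was also 3.

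**Step 5: what a difference of 5 does to the comparison.** Suppose PEP has 20 of its 35 students in period 1 and control has 15 of its 35. If mean change over the trial differs by δ between the two periods for reasons unrelated to PEP, the arm comparison shifts by (20/35 − 15/35)δ = 0.14δ. The sign is random, so this is extra variance and not a systematic error. The article gives nothing from which to put a value on δ.

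**The case against.** Several points on the other side stand and limit the claim.

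- **The premise is conditional.** A reader might infer that PEP has to run inside each class's own PE period. The article says only that scheduled periods are used. If all PEP students share a common slot, 35 make two sessions of 17 and 18 with or without stratification.
- **Enrolment order is unknown.** Class-by-class enrolment nearly removes the problem. But the article does not commit to that order, so this protection would be accidental.
- **Chance imbalance is not bias.** A reader might infer that uneven classes, ages or body sizes would bias the PEFR or walking-test result. With concealed randomisation they do not in expectation. Moreover, baseline is one of the time levels, so stable differences in level between students largely drop out of the group-by-time test. Only influences on change remain.
- **Staff differences are beyond reach.** Whoever leads PEP and whoever leads standard PE may differ after any allocation. Stratification cannot alter that, and the Limitations section already discloses it.
- **Session size is approximate and depends mainly on timetabling.** Exceeding 20 by one is hardly a failure, hence the 6% figure for 14–21. At the article's own 20% attrition, a group of 17.5 falls to 17.5 × 0.80 = 14 even if perfectly stratified.
- **The stated method is legitimate.** Unstratified blocks do what the article claims for them, and the design is an accepted one.

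None of this answers the central point: a class-level influence is acknowledged, and a nearly free way to balance it goes unused in both the list and the model.

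**Conclusion.** The point holds as a design improvement worth making. It is not an error that invalidates the trial. The allocation leaves the split within PE periods or classes to chance whenever there is more than one of them and enrolment is mixed.

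Under the assumption of two periods of 35, the arms differ by 5 or more within a period in about 37% of trials, and a PEP group leaves the 15 to 20 range in about 17%. Under class-by-class enrolment, differences of 5 or more fall below 1%. The true figure depends on period counts and enrolment order that the article does not give.

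The consequence is some loss of precision and possibly uneven groups. The documents do not support a claim of biased treatment effects, of arms made comparable in delivering staff, or of session sizes secured by stratification alone.

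**What to change.** In Randomization and blinding, state that allocation is stratified by PE period (or class), with a separate list in blocks of 4 and 6 and a separate envelope series for each stratum. In Data analysis, include the stratum as a between-student factor in the repeated-measures model together with its interaction with time, since that interaction is the part that bears on the group-by-time test. In Intervention, one sentence on how many periods are used and how PEP groups are formed from them would show whether 15 to 20 is attainable.

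The cost is one setting in the list generator, one more envelope series per stratum and a few degrees of freedom, with no extra students, visits or staff. The downside is an incomplete last block in each stratum, giving an arm difference of at most 3 there. Because the envelopes are prepared before enrolment, the change is cheap only if made before that.
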